# STABLE trial of spectacle provision and driving safety among myopic motorcycle users in Vietnam: study protocol for a stepped-wedge, cluster randomised trial

**DOI:** 10.1186/s13063-024-08644-2

**Published:** 2024-12-18

**Keywords:** Road traffic crash, Naturalistic driving, Myopia, Motorcycle, Stepped-wedge randomised trial, Vietnam

## Abstract

**Background:**

Traffic crashes are the leading cause of death globally for people aged 5–29 years, with 90% of mortality occurring in low- and middle-income countries (LMICs). The STABLE (Slashing Two-wheeled Accidents by Leveraging Eyecare) trial was designed to determine whether providing spectacles could reduce risk among young myopic motorcycle users in Vietnam.

**Methods:**

This investigator-masked, stepped-wedge, cluster randomised naturalistic driving trial will recruit 625 students aged 18–23 years, driving ≥ 50 km/week, with ≥ 1-year driving experience and using motorcycles as their primary means of transport, in 25 clusters of 25 students in Ho Chi Minh City, Vietnam. Motorcycles of consenting students who have failed self-testing on the WHOeyes app will be fitted with Data Acquisition Systems (DAS) with video cameras and accelerometers. Video clips (± 30 s) of events flagged by the accelerometer will be reviewed for crash and near-crash events per 1000 km driven (main outcome). Five clusters of 25 students will be randomly selected every 12 weeks to undergo ocular examination and an estimated 40% of these will have bilateral spherical equivalent < − 0.5 D, and better-eye presenting distance visual acuity < 6/12, correctable bilaterally to ≥ 6/7.5. They will be given free distance spectacles and their driving data before receiving spectacles will be analysed as the control condition and subsequent data as the intervention condition. Secondary outcomes include visual function, cost-effectiveness and self-reported crash events.

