### Study design

STABLE was designed as a SW-CRT because of the ethical concerns inherent in failing to deliver spectacles immediately to persons identified with uncorrected myopia and engaged in a potentially dangerous activity such as driving a motorcycle, as would occur in a traditional trial. The stepped-wedge design involves the sequential transition of clusters from control to intervention conditions in randomised order at 12-week intervals, with spectacles delivered to those needing them as soon as uncorrected myopia is detected. After all participant clusters have undergone vision testing and refraction, all eligible participants will have been exposed to the intervention. This approach balances the ethical requirement to avoid withholding treatment from known myopic drivers and the need to conduct a randomised evaluation of the intervention.

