As shown in Fig. 1, all potential participants enter in the control condition and will have DAS units installed on their motorcycles. However, as they have not yet been examined and refracted, the identity of actual trial participants is not known at that time. Subsequently, during the 14 days before each 12-week period, participants in five randomly selected clusters will undergo an eye examination and refraction. Those meeting the following criteria will receive spectacles within 1 week of the examination and transition to the intervention condition, and their previously collected DAS information will be analysed as control data:Presenting distance visual acuity < 6/12 in the better-seeing eye due to un- or under-corrected myopiaVision correctable with glasses to 6/7.5 or better in both eyesAt least 0.5 D of myopia in both eyes

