### Sample size

Unpublished data from Dynamic Vision, an organisation currently collecting CNC events from motorcycle drivers in Vietnam, were used to inform the power calculation. Results showed an estimated mean event rate of 1.67 CNC events per 1000 km driven (standard deviation [SD] = 0.556). For a postulated, clinically meaningful 10% reduction in CNC events, a stepped-wedge cohort design comprising six sequences of seven myopic participants per cluster (a 28% prevalence, below the 40% figure observed during pilot testing with the WHOeyes app), a coefficient of variation of cluster sizes of 3, and five clusters per sequence with Individual Auto Correlation (IAC) of zero, confer 90% power (mean difference = 0.167, SD = 0.556; intraclass correlation [ICC] = 0.02 [0.01–0.05]) [23]. This would be achieved by collecting DAS data from 175 students over the course of 72 weeks. To achieve this, 5200 students will be invited to self-assess their vision using WHOeyes. Pilot data indicate that approximately 12%, or 625 students, will fail that assessment and be eligible to join the preliminary phase of the study, with placement of DAS units on their motorcycles. An estimated 250 (40% of those failing the WHOeyes self-assessment) will have eligible, uncorrected/under-corrected myopia detected on their subsequent eye examination by an optometrist. They will then be assigned to the intervention condition and given free spectacles. With a 30% dropout rate, this will result in complete datasets for 175 participants over the course of the trial.

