### Additional data collection

The following information will be collected by questionnaire from those who fail the WHOeyes self-assessment in at least one eye: age, driving experience, primary means of transport, distance driven per week, motorcycle type, brand, model and engine capacity, and possession of a driving licence. Those meeting the inclusion criteria for DAS fitting and providing informed consent will be asked to provide the following baseline data: exposure to eyecare assessments at time of licensure, visual function (VFQ-25) [22], driver risk profile (Dula Dangerous Driving Index [DDDI]) [24] and economic data including home location (urban or rural), income and estimated monthly expenditures. At the time of the eye examination but before the participant’s cluster transitions to the intervention condition, data will be collected on visual acuity, refractive error, details of current spectacle wear, presence of ocular abnormalities and whether spectacles are required. Data will subsequently be collected on whether spectacles are provided.

Every 2 weeks, participants meeting with study staff to exchange the removable drive in their DAS units will be asked whether they have been involved in a crash in the preceding 2 weeks. Repair and insurance costs will be recorded if a crash occurs. Financial data for the cost-effectiveness calculations from a societal perspective will be captured, including cost of health care received and for crash-related repairs.

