### Statistical analyses

All outcomes for trial participants will be analysed in accordance with the intention-to-treat (ITT) principle. Baseline characteristics will be summarised using means and standard deviations, medians and interquartile ranges, or numbers and percentages, as appropriate. The primary outcome (number of CNC events per 1000 km driven) will be analysed using generalised linear mixed models, reporting mean differences and adjusting for cluster, secular and time effects. For example, secular trend adjustments will take into consideration national and regional driving safety campaigns and calendar time. Seasonal factors (amount of daylight, inclement weather, etc.) are likely to play a role in the number and severity of CNC events. Analysis of secondary outcomes will be done in a similar fashion. Risk differences for binary outcomes and mean differences for continuous outcomes, all adjusting for cluster, secular and time effects, will be reported.

Sensitivity analyses will be conducted to examine the intervention effects, adjusting for additional pre-specified potential confounders including age (years as a continuous variable), DDDI risk profile [24] (total score as a continuous variable) and residence (rural/urban as a binary variable).

Missing data will likely result when participants withdraw from the study or do not complete the full follow-up. Multiple imputations of missing data when assessing secondary outcomes will involve creating 20 copies of the data and imputing missing values by chained equations before averaging the datasets [26].

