### Protocol compliance

A protocol deviation is defined as a failure to adhere to the protocol, such as delivering an incorrect intervention or errors in applying eligibility criteria. Major protocol deviations constitute instances where enrolled participants have not provided informed consent or deliberately provide incorrect data. Other protocol deviations include situations where participants are incorrectly randomised, or where participants in the intervention condition have not receive the prescribed spectacles.

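### The protocol defines the control/intervention boundary in two conflicting ways: by each rider's receipt of spectacles and by the cluster's randomised transition

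*Protocol article*

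**What the plan says.** Two places put the boundary at the level of the rider:

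- Abstract, Methods: "their driving data before receiving spectacles will be analysed as the control condition and subsequent data as the intervention condition". This is the only sentence that names receipt of spectacles as the analysis boundary.
- Participants and recruitment procedure: "Those meeting the following criteria will receive spectacles within 1 week of the examination and transition to the intervention condition". It adds that the DAS data recorded up to then serve as control data.

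The other places point to the cluster, or separate assignment from receipt:

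- Study design: "The stepped-wedge design involves the sequential transition of clusters from control to intervention conditions in randomised order at 12-week intervals".
- Randomisation, allocation and concealment: clusters are what is randomly selected, and a transition date is named for them.
- Additional data collection: examination data are gathered before the participant's "cluster transitions to the intervention condition".
- Sample size: "They will then be assigned to the intervention condition and given free spectacles". Assignment is stated alongside receipt and does not depend on it.
- Statistical analyses: "All outcomes for trial participants will be analysed in accordance with the intention-to-treat (ITT) principle". The section defines neither the exposure variable nor its switch date.
- Protocol compliance: one listed deviation is that "participants in the intervention condition have not receive the prescribed spectacles".

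**The concern.** Only the step at which a cluster crosses is randomised. When, or whether, an eligible rider in that cluster obtains spectacles is not. Under the Abstract's rule, a rider who attends late, declines or never collects spectacles goes on contributing control data after the cluster has crossed. Within that cluster and period, part of the contrast is then between riders who collected and riders who did not. If the two groups differ in riding risk, the difference enters the treatment effect, with a sign nobody can predict.

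The deviation listed under Protocol compliance cannot arise under the Abstract's rule, because a rider who never received spectacles would never enter the intervention condition. An analyst following the Abstract and one following Study design, Statistical analyses and Protocol compliance would code the exposure variable differently. The first could not properly report the result as intention-to-treat.

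**Working it through.** **1. The plan's own figure.** Inputs from Sample size: difference 0.167 (10% of 1.67), SD 0.556, ICC 0.02, IAC 0, 5 clusters per sequence, 7 riders per cluster. Assumed, because not stated: two-sided alpha 0.05 and cluster autocorrelation 1. The model is a stepped-wedge linear mixed model with fixed period effects, 5 crossover steps, 6 periods (72/12) and equal cluster sizes, which gives 25 x 7 = 175 riders. The standard error is 0.0518 and the power is Phi(0.167/0.0518 - 1.96) = 89.7%, against the stated 90%. The model is therefore a fair base for the rest.

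**2. Bias if condition followed receipt.** Set-up: 25 clusters of 10 eligible riders (the plan's 250), no true effect, and 1 rider in 10 never receives spectacles. Non-receivers have a rate higher by e x 1.67 in every period. The non-receipt rate and e are assumptions. The covariance within a cluster is

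V = 0.556^2 x [0.02 for any two observations in the cluster + 0.98 x (rho for the same rider in different periods, 1 for the same observation)].

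The expected coefficient is (sum X'V^-1 X)^-1 (sum X'V^-1 E[y]). The exposure column of X is 0 throughout for non-receivers under receipt coding, and 1 from the cluster's crossover under cluster-date coding. The share of trials significant at 5% follows from bias/SE.

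| Rider correlation rho | SE | Bias, e = 30% | Significant | Bias, e = 10% | Significant |
|---|---|---|---|---|---|
| 0.073 | 0.0403 | -0.133 (-8.0%) | 91% | -0.044 (-2.7%) | 20% |
| 0.3 | 0.0382 | -0.065 (-3.9%) | 40% | -0.022 (-1.3%) | 9% |
| 0.6 | 0.0305 | -0.026 (-1.6%) | 14% | -0.009 (-0.5%) | 6% |

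Percentages in brackets are of the mean rate 1.67. If non-receivers are safer by the same amount, the sign reverses. Under cluster-date coding the expected coefficient is 0 in every row.

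**3. Why the table does not start at rho = 0.** The planning IAC of 0 would give -0.176 (-10.5%) at e = 30%. But a stable 30% excess (0.3 x 1.67 = 0.501) in a tenth of riders itself creates between-rider variance of 0.1 x 0.9 x 0.501^2 / 0.556^2 = 0.073 of the total. So rho cannot be 0 in that scenario, and 0.073 is its lower end. For e = 10% the same formula gives 0.008, and the bias at rho = 0 would be -3.5%.

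**4. What cluster-date coding costs.** Examinations fall in the 14 days before the period and spectacles follow within 7 days, so planned receipt runs from day -14 to day +7.

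- Uniform timing (assumed): receipt averages -7 + 3.5 = -3.5 days, made up of 4.1 days early and 0.6 days late per rider. A true 0.167 is estimated as 0.161, a loss of about 3.5%.
- Every rider 7 days late (7/84 = 8.3% of the first exposed period): 0.158, a loss of 5%, with power 86.4%.
- Every rider supplied on day -14 (14/84 = 16.7% of the last control period): 0.150, a loss of 10%. This is a bound, since examinations are spread over the fortnight.
- Non-receipt of 5%, 10% or 20% (assumed), 7 riders per cluster: the effect becomes 0.167 x (1 - p) and power is 86.5%, 82.7% or 73.3%.

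**The case against.** The strongest reply is that the plan already points to cluster-based coding. Study design and Additional data collection speak of clusters crossing, Statistical analyses promises intention-to-treat without naming receipt as the exposure, and the only provision on non-receipt leaves such riders in the intervention condition. The Abstract sentence may be shorthand for the planned order of events, and the sentence in the recruitment section can be read the same way. Detailed exposure coding commonly belongs to the SAP, which is not shown.

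Much of this stands. A reader might infer that the primary analysis is as-treated and that riders without spectacles are counted as controls after crossover. The documents do not settle the first point, and no passage states the second, which follows only from a literal reading of the Abstract. Nor do riders found ineligible at examination become controls, because their data are dropped.

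The reply also holds on size. The documents give no non-receipt rate and no risk gap. Spectacles are free and due within a week, and staff meet riders every 2 weeks, so heavy non-collection is not the obvious default. The IAC of 0 is a planning input, and the analysis model is not bound to it.

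The reply does not remove the conflict. The Abstract states a rule about analysis, which goes beyond leaving a detail open, and that rule is incompatible with the intention-to-treat statement and with the listed deviation.

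**Conclusion.** The point holds as an inconsistency in how condition is defined. Two places tie the boundary to the rider, one of them expressly to receipt of spectacles. The design, randomisation, data-collection, analysis and compliance sections support the cluster's randomised transition.

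If the receipt rule were used, the estimate would be open to selection bias of unknown sign. With 10% non-receipt the size is about 0.5% to 8% of the mean event rate for risk gaps of 10% to 30% and rider correlations of 0.07 to 0.6. The trial is designed to detect a 10% reduction, so the upper end would matter and the lower end would hardly be noticed. These figures are illustrations that rest on assumed non-receipt and risk gaps, and they do not predict what this trial would show. Cluster-date coding has no such bias under any of these assumptions.

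**What to change.** State in the Abstract, in Participants and recruitment procedure and in Statistical analyses that, for every eligible rider, condition in the primary analysis is set by the randomised transition date of the rider's cluster, regardless of whether or when spectacles were received. Keep receipt-based coding as a sensitivity analysis labelled as-treated. Make the change before outcome data are seen, and carry the same definition into the SAP.

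Leaving out one common window per cluster, from the opening of the examination fortnight to 7 days after the transition date, is optional, for example as a further sensitivity analysis. It would remove the timing dilution at the price of 21 of 504 days (4.2%) of riding.

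The cost is a few sentences and no new data. The downside is some dilution of the effect: about 3% to 5% from delivery timing under the schedules considered plausible above, plus a share equal to the non-receipt rate.

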**Discussion:**

STABLE will be the first randomised trial of vision interventions and driving safety in a LMIC.

**Trial registration:**

ClinicalTrials.gov, NCT05466955. Initial registration: 20 July 2022, most recent update: 9 July 2024.

## Introduction

Road traffic crashes are the leading cause of death globally among people aged 5 to 29 years and are predicted to become the seventh most-common cause of all-age mortality by 2030 [1, 2]. Though only 60% of the world’s cars are driven in low- and middle-income countries (LMICs), 90% of traffic crash mortality occurs there [1]. Southeast Asia trails only Africa as the global region with the highest burden of traffic mortality, with 20.7 fatalities per 100,000 population [3]. Drivers aged < 25 years are 15 to 33 times more likely to crash than older drivers [4]. More than 80% of Vietnamese households own at least one motorcycle, which comprise 93% of registered motor vehicles in the country [5]. Southeast Asia is the global region with the highest number of deaths associated with motorcycle use, accounting for 43% of global fatalities, with Vietnam, where motorcycles are involved in over two-thirds of road fatalities, having one of the region’s highest rates of motorcycle-related mortality [3].

Myopic refractive error is the leading cause of distance vision impairment globally and is steadily increasing [6]. Southeast Asia has the highest prevalence of adult myopia (32.9%) of any World Health Organisation (WHO) sub-region [7]. It is estimated that half the world’s population will have myopia by 2050 [8–10]. Uncorrected myopia among young adults in Vietnam, the age group at greatest risk for road traffic death, accounts for 93% of all vision impairment [11, 12]. Although myopia can be safely, effectively and inexpensively treated with spectacles, rates of spectacle ownership among young people who need them are as low as 15–20% in low- and middle-income countries (LMICs) [13, 14].

Good vision is widely perceived to be essential for safe driving, as reflected in motor vehicle licensure laws that require distance vision of a certain standard before receiving a driver’s licence in many countries. However, there is little evidence from existing interventional studies that improving vision enhances traffic safety. Systematic reviews based primarily on studies from high-income countries have largely failed to detect a strong association between central vision and crash risk [15]. However, the situation appears to be different in LMICs. A recent meta-analysis by Piyasena et al. of 13 studies from LMICs revealed a 46% increased risk of road traffic crashes among drivers with impaired central visual acuity (risk ratio [RR] 1.46, 95% confidence interval (CI) 1.20 to 1.78, *p* < 0.001) and a high prevalence of poor vision among drivers in such settings [16]. Although some studies have investigated the impact of vision correction on driving performance [17–19], the review by Piyasena et al. found no randomised trials of vision and driving safety in LMICs [16].

The STABLE (Slashing Two-wheeled Accidents by Leveraging Eyecare) randomised trial was designed in collaboration with the Vietnamese Ministry of Transportation to address these evidence gaps by assessing the hypothesis that the provision of spectacles to young myopic motorcycles drivers in Vietnam can reduce the rate of crash and near-crash (CNC) events, as measured by on-board Data Acquisition Systems (DAS) under conditions of naturalistic driving.

## Materials and methods

STABLE is an investigator-masked, parallel-group, naturalistic driving study using a superiority, stepped-wedge, cluster randomised trial (SW-CRT) design, with faculties within participating universities as the clusters.

### Study design

STABLE was designed as a SW-CRT because of the ethical concerns inherent in failing to deliver spectacles immediately to persons identified with uncorrected myopia and engaged in a potentially dangerous activity such as driving a motorcycle, as would occur in a traditional trial. The stepped-wedge design involves the sequential transition of clusters from control to intervention conditions in randomised order at 12-week intervals, with spectacles delivered to those needing them as soon as uncorrected myopia is detected. After all participant clusters have undergone vision testing and refraction, all eligible participants will have been exposed to the intervention. This approach balances the ethical requirement to avoid withholding treatment from known myopic drivers and the need to conduct a randomised evaluation of the intervention.

### Participants and recruitment procedure

The research team will formally engage with the Board of Executives of selected universities in Ho Chi Minh City, explaining the study’s objectives and extending invitations for their participation. The study will be advertised via posters, email and the fan pages of either the Department of Student Affairs or the Student Union at each enrolled university. To encourage recruitment, advertisements for STABLE will include a brief description of the incentives for participation (VND 220,000 or approximately US$9 per student per month for the duration of involvement in the study) and free spectacles for participants identified with uncorrected myopia (see below).

Prior to recruitment, potential student participants will be asked to conduct a smartphone-based vision self-assessment using WHOeyes, the WHO’s free smartphone application for vision monitoring available in Vietnamese [20, 21]. Those failing that assessment (an estimated 40% based on pilot testing who have distance visual acuity in either eye < 6/12, with normal near visual acuity in both eyes) are at increased risk of refractive error and will be invited to join the pre-evaluation phase of the study. Students providing informed consent and meeting the initial inclusion criteria below on a brief survey will have DAS devices fitted to their motorcycles. These instruments are equipped with front and rear, driver-facing video cameras and accelerometers, and can detect changes in speed and direction (such as swerving).Enrolled in one of the selected faculties of a participating universityAged 18 to 23 yearsSole driver of their motorcycleUse their motorcycle as their primary means of transportDrive ≥ 25 km/week by self-reportHold a valid driving licence if required (for motorcycles having an engine capacity > 50 cc)Failed the WHOeyes vision self-assessment in at least one eye

As shown in Fig. 1, all potential participants enter in the control condition and will have DAS units installed on their motorcycles. However, as they have not yet been examined and refracted, the identity of actual trial participants is not known at that time. Subsequently, during the 14 days before each 12-week period, participants in five randomly selected clusters will undergo an eye examination and refraction. Those meeting the following criteria will receive spectacles within 1 week of the examination and transition to the intervention condition, and their previously collected DAS information will be analysed as control data:Presenting distance visual acuity < 6/12 in the better-seeing eye due to un- or under-corrected myopiaVision correctable with glasses to 6/7.5 or better in both eyesAt least 0.5 D of myopia in both eyes

